**Flow of participants through the**
***Get Moving***
**Trial.**

### Recruitment

Individuals working or studying on the Cambridge Biomedical Campus (including Addenbrooke’s Hospital, Cambridge, UK) aged 18–65 years were eligible to take part in the study. Contact was made with each institution on the Biomedical Campus to establish an appropriate contact, who was asked to circulate a generic advert to staff and students, via newsletter, email, posters and/or via their institution’s intranet, with the aim of reaching all staff and students on the Campus. Recruitment stands were run in areas frequented by staff and students, e.g. staff canteen and lobby areas. Individuals who registered an interest in taking part in the study were sent an information sheet about the study and a brief questionnaire to complete and return to assess the first of a three stage eligibility assessment process (excluded if physically active (scoring ≥30 on the Godin Leisure-Time Exercise Questionnaire (GLTEQ) for moderate-to-vigorous activities [24]); were instructed by their GP not to engage in regular physical activity; were unable to walk briskly on the flat for 15 minutes without help). If an individual met this stage of eligibility criteria, they were contacted by telephone to go through the second stage of eligibility screening (excluded if they were participating in another clinical randomised trial; taking ≥100 mg/day of Atenolol or an equivalent amount of another beta-blocker; were pregnant; planning on leaving their position on the Biomedical Campus within 4 months of recruitment; did not have access to or were unable to operate an internet-connected home PC running the minimum specification requirements set by Imperative; or could not use an English-language website). Potential participants who remained eligible discussed participation in the trial in more detail with the study team by telephone and were given the opportunity to ask questions prior to booking an appointment to attend for baseline measures.

#### Baseline assessment

On arriving at the measurement centre, having fasted for the preceding one hour (including abstaining from nicotine, caffeine and vigorous exercise), individuals provided fully informed written consent following a discussion about the study with the measurement team. Height, weight and blood pressure were measured first to check the third stage exclusion criteria (individuals whose BMI was ≤18 kg/m^2^, or who had a mean blood pressure ≥160/100 mmHg – those routinely excluded by the Imperative Health system as a safety precaution). This was explained to potential participants prior to their attendance at the measurement visit in the information sheet and also during the telephone call. Individuals who met all inclusion criteria continued with the visit. All baseline information was collected prior to randomisation. Participants had anthropometric and biological measurements taken (see Measures section and Table 1 for further details). Participants then completed a treadmill exercise test which was terminated when 80% of their age-predicted maximum heart rate (i.e. 208 minus 0.7*age) was reached. Predicted maximal cardio-respiratory fitness (VO_2max.pred_) was estimated using extrapolation of the heart-rate to VO_2_ relationship to age-predicted maximal heart rate. Participants were asked to provide demographic information and to complete a number of questionnaire measures (see Measures section and Table 1). Anthropometric and clinical measurement values were concealed from participants unless they specifically asked to see the results, thereby minimising the possibility of behaviour change associated with clinical feedback and to maximise participant retention at follow-up. Before leaving the measurement centre, participants were fitted with a combined movement and heart rate monitor (Actiheart, CamNtech, Cambridge, UK) and were instructed to wear the monitor for six days and nights continuously. They were instructed on how to change ECG electrodes (supplied), both verbally and in writing with depiction of correct placement. In the event that an insufficient amount of valid data was collected from the combined monitor following two separate wear periods, the participant was not able to continue in the study.

**Table 1 Tab1:** **Measures used in the Get Moving Trial**

**Measure(s)**	**Screening**	**Baseline visit**	**12-week follow-up visit**	**Post 12-week follow-up**
**Co-primary outcome measures**				
Physical activity		*√*	*√*	
Cardiorespiratory fitness		*√*	*√*	
**Anthropometric measures**				
Height		*√*		
Weight		*√*	*√*	
Waist circumference		*√*	*√*	
Body fat %		*√*	*√*	
**Biological measures**				
Blood pressure, heart rate, ECG (done at follow-up for participants that need a medical review), HbA_1c_, fructosamine, total cholesterol, HDL- and LDL-cholesterol, triglycerides, plasma vitamin C		*√*	*√*	
**Degree of intervention use**				
Paper-based physical activity diary use (Diary group)				*√*
Use of physical activity band from Imperative Health (Activity Band & Activity Band Plus groups)				*√*
No. of times the Imperative Health website was visited (Activity Band & Activity Band Plus groups)				*√*
**Demographic measures**				
Date of birth	*√*	*√*		
Sex	*√*	*√*		
Living situation		*√*		
Number of children in household		*√*		
Highest education level		*√*		
Ethnic origin		*√*		
**Psychological measures**				
Theory of planned behaviour questionnaire		*√*		
Theory of planned behaviour monitoring questionnaire (post-randomisation questionnaire)	Completed two weeks post randomisation			
Conscientiousness questionnaire		*√*		
**Self-reported health behaviours**				
Recent physical activity (R-PAQ)			*√*	
Functional status (SF-8)		*√*	*√*	
Perceived stress (4-item PSS)		*√*	*√*	
Self-report habit index questionnaire		*√*	*√*	
Gym membership		*√*	*√*	
Smoking status		*√*	*√*	
Vitamin supplement use		*√*	*√*	
Prescribed medications		*√*	*√*	
Frequency of self-weighing		*√*	*√*	
**Other questionnaires/single-item questions**				
Godin Leisure-Time Exercise Questionnaire (GLTEQ)	*√*			
Participating in other research	*√*			
GP advised against doing physical activity	*√*			
Beta-blocker use	*√*			
Pregnancy status	*√*			
Able to walk briskly for ≥15 minutes	*√*			
Access to and ability to use a home PC and internet	*√*			
Ability to use an English language website	*√*			
Leaving job in next 16 weeks	*√*			
Self-report of doctor diagnosed diabetes		*√*	*√*	
Rose Angina questionnaire		*√*	*√*	
Main study goal		*√*		
Job satisfaction			*√*	
Contact with other study participants (yes/no)			*√*	
Self-monitoring behaviour			*√*	
Use of physical activity advice websites (yes/no)			*√*	
Satisfaction with study participation				*√*
Programme evaluation questionnaire				*√*
Absence from work due to illness			*√*	

#### Randomisation, allocation concealment and blinding

Once the combined monitor had been returned and the recorded data checked for quality and quantity (≥35 hours), participants were randomly allocated to one of the four study groups (Control, Diary, Activity Band or Activity Band Plus). Randomisation lists were prepared using Stata [25] within strata defined by age (<45, ≥45 years), sex and BMI (<27, ≥27 kg/m^2^) using a block size of 8. Participants in the ‘Control’ and ‘Diary’ groups were sent their randomisation allocation by internal post. Participants in the ‘Activity Band’ and ‘Activity Band Plus’ groups were told their allocation at their place of work and were given the necessary equipment and instructions on how to proceed during the 12 week intervention. The measurement team were blinded to the participants’ group allocation throughout the trial.

#### Interventions

##### Control group

Participants randomised to this group received no intervention.

##### Diary

Participants were given a pocket-sized, paper-based physical activity diary and advised to record, on a daily basis, each time they engaged in physical activity for the duration of 10 minutes or more. Participants were instructed to record whether they undertook any activity (yes/no), the type of activity undertaken, the time they began the activity and its total duration, for the entire 12 week intervention period.

##### Activity band with web-based feedback (Activity Band)

Participants in this group were issued with a physical activity accelerometer (Activity Band, Imperative Health, AXA ICAS Limited, East Sussex, UK) and were asked to start using the band to monitor their physical activity. The Activity Band is a wrist-worn device containing a tri-axial accelerometer similar to the one described by Esliger et al. [26]. It is able to store movement data for up to two weeks until it is uploaded via Bluetooth to the Imperative Health website, which displays the physical activity data in graphical format. Participants were instructed to activate their account within one week of receiving the intervention and to log on to their account to upload their movement data and view their activity graphs at least once per week. The activity graphs numerically and graphically show the number of minutes of physical activity undertaken each day, each week and each month, separated into three different activity intensities (moderate, high and very high intensity activity). If no account activity was detected for a continuous period of 15 days, Imperative Health liaised with the study team who contacted the participant to find out if they were experiencing any technical problems with the programme or were no longer interested in receiving the intervention. (Figure 2).

**Figure 2 Fig2:**
[figure not shown]
**Example of an Activity graph.**

##### Activity band with web-based feedback plus online coaching engine (Activity Band Plus)

Participants in this group were provided with the same physical activity band as the ‘Activity Band’ group (see above). In addition, participants were provided with a Bluetooth enabled weighing scale to enable self-monitoring of body weight; access to the nutritional component of the program for monitoring calorie intake, and access to the full Imperative Health online coaching engine (http://www.imperativehealth.com). The coaching engine is a web-based automated dialogue system which serves as a “virtual coach” to help individuals change their health-related behaviours. Earlier versions of Imperative have been tested in previous studies [27,28]. This system provides a more interactive experience for participants compared with the ‘Diary’ only and the ‘Activity Band’ intervention groups. As with the ‘Activity Band’ group, participants were instructed to activate their account within one week of receiving the intervention and to log on to their account to upload their movement data and view their activity graphs at least once per week. The system uses the activity data from the physical activity band and the weight data from the Bluetooth-enabled weighing scales to provide numerical and graphical feedback to the user regarding their progress. The system also contains structured daily meal plans, a food diary for recording all food and drink consumed, a physical activity planner to help with planning structured exercise, progress graphs with physical activity levels and weight loss goals displayed in graphical format, and a tailored message service which provides reminders for exercise and feedback to encourage the setting and meeting of goals. Participants were advised to use as many of these elements as they desired, but full engagement was encouraged. As with the ‘Activity Band’ group, if no account activity was detected for a continuous period of 15 days then Imperative Health liaised with the study team, who contacted the participant to find out if they were experiencing any technical problems with the programme or were no longer interested in receiving the intervention.

#### Post-randomisation questionnaire

All participants, irrespective of study group allocation, were sent a questionnaire by email two weeks after the date of randomisation to assess the determinants of monitoring behaviour and were asked to complete and return it to the study team. See Measures section for details of content.

#### Follow-up assessment

Approximately eight weeks post-randomisation, participants were contacted by telephone by a member of the study team to arrange a convenient date and time to attend for a follow-up visit approximately 12 weeks post-randomisation. At week 10 participants were asked to wear the combined movement and heart rate monitor for six days and nights continuously and to return it to the study co-ordination office along with any intervention equipment prior to their 12-week visit (to ensure the measurement team remained blinded to the intervention allocation). Participants were asked not to mention their randomised group to the measurement team at the follow-up visit. In the event that an insufficient amount of valid data was collected from the combined monitor, the participant was provided with another monitor at their follow-up visit to wear for the following six days and nights.

As for the baseline visit, all participants fasted for one hour (including abstaining from nicotine, caffeine, and vigorous exercise), had anthropometric and biological measurements taken, completed a sub-maximal treadmill test and were asked to complete questionnaire measures (see Table 1).

If, after repeated efforts to book a convenient appointment, a participant was unable to attend for their follow-up measurement visit, a postal alternative was offered which included questionnaires and the combined monitor for self-attachment. Participants who needed a repeat blood test (samples lost or degraded or insufficient blood volume taken) were offered the opportunity to return for a repeat blood test or to have the test repeated at their GP surgery. Participants agreeing to complete postal measures were followed up for a maximum of six months, after which time the participant was classified as ‘lost to follow-up’.

#### Programme evaluation questionnaire

A randomised group-specific evaluation questionnaire was sent to all participants by email after attending their follow-up visit (again to maintain blinding of the measurement team taking follow-up measures). See Measures section below for details of content.

#### Health report

After receipt of the evaluation questionnaire, all participants were sent a health report containing their physiological and clinical measurements (including measures of fitness and physical activity, blood pressure, weight, BMI, body fat percentage, waist circumference, blood glucose and total cholesterol levels) from both their baseline and 12 week visits. A copy of this report was also sent to their GP for information, together with the clinical results from both visits.

#### Measures

Table 1 shows the measures taken at each stage.

##### Cardiorespiratory fitness and free-living physical activity (co-primary outcome measures)

Cardiorespiratory fitness was assessed at baseline and again at 12 weeks using a ramped treadmill protocol consisting of three phases, as described elsewhere [23]. In brief, *Phase 1* (level walking) involves level walking with increasing speed (3 min at 3.2 km/h and then accelerating at 0.33 km/h/min for the next 6 min), *Phase 2* (graded walking) consists of brisk walking (5.2–5.8 km/h) with increasing gradient (at a rate of 1.7% increased gradient/min for 6 min), and *Phase 3* (level running) involves level running with the treadmill speed increasing from 9 to 12.6 km/h for 4.5 min (average acceleration of 0.78 km/h/min). Transition between *Phase 2* and *3* entails a change in gradient of −10.2% over 30 seconds (to a level gradient), followed by a change in speed of +3.2 km/h over 30 seconds. The protocol finishes with a two minute standing recovery. The treadmill protocol is terminated early in the event that the participant wishes to stop or if 80% of the age-predicted maximal heart rate of the participant is exceeded. Energy cost (oxygen consumption) of this protocol is predicted from time (speed and incline) as reported elsewhere [23]. Cardiorespiratory fitness was estimated by extrapolation of the heart rate/oxygen consumption relationship to age-predicted maximal heart-rate. We only used data up to the time point which denotes the lowest common denominator between the baseline and follow-up visit for each participant.

Free-living physical activity was assessed at baseline and again at 12 weeks using combined sensing, following the pre-processing of the heart rate trace [29]. Data from the fitness test (see above) was used to individually calibrate heart-rate [23], and combined with acceleration in a branched equation framework [22] to estimate activity intensity (J/min/kg). Resulting time-series data are summarised as PAEE (kJ/kg/day) and time spent in sedentary (SED, in hours/day) and moderate-to-vigorous intensity physical activity (MVPA, in min/day), whilst minimising diurnal information bias caused by non-wear periods (segments of non-physiological data). Participants without individual calibration data have their free-living data processed using an age, sex, beta-blocker and sleeping heart rate adjusted group calibration equation for the translation of heart rate into activity intensity.

##### Anthropometric measures

Height was measured without shoes using a wall-mounted fixed rigid stadiometer. Weight and body fat percentage were measured using a bio-electrical impedance monitor without shoes and in light indoor clothing (Tanita BC-418MA). Waist circumference was estimated as the mean of two measurements taken with a D-loop measuring tape placed halfway between the lowest point of the rib cage and the anterior superior iliac crest with the participant in a standing posture and in light indoor clothing. If the two measurements varied by more than 3 cm a third measurement was taken and the mean of the three measures used.

##### Biological measures

Blood pressure and heart rate were calculated based on the mean of three measurements performed after 10 minutes of rest, with participants in a seated posture using an automatic sphygmomanometer (Omron) with the cuff placed on the dominant arm at the level of the heart. A resting electrocardiogram (ECG) was taken using a 12-lead ECG (Seca CT6i/CT6Pi).

Dietary intake of fruits and vegetables was assessed by plasma vitamin C levels. As humans are unable to synthesise vitamin C, and because the main source of vitamin C in the Westernised diet is fruits and vegetables [30], vitamin C levels provide an objective measure of dietary intake [31]. Plasma vitamin C was measured in venous blood collected into citrate tubes using a closed blood collection system (Monovette, Sarstedt, Germany). The plasma was then stabilised in a standardized volume of metaphosphoric acid and stored at −80°C. Plasma vitamin C concentration was measured using a fluorometric assay in monthly batches based on a method described by Vuilleumier & Keck [32] (PerkinElmer Victor 3 Plate reader).

HbA_1c_ was analysed in fresh blood by ion-exchange high-performance liquid chromatography (Tosoh G7 Haemoglobin Auto-analyser before August 2013 and Tosoh G8 Haemoglobin Auto-analyser after). Serum total-, LDL- and HDL-cholesterol and triglycerides were measured in fresh blood by enzymatic techniques (Dimension RxL Max Clinical Chemistry System (Siemens Healthcare Ltd) before December 2013 and Advia 2400 Chemsitry System (Siemens Healthcare Ltd) after). Serum fructosamine was analysed in monthly batches in serum stored at −80°C using an enzymatic method supplied by Randox, modified to run on the Siemens Dimension RXL. All biochemical analyses were conducted on venous blood collected using a closed blood collection system (Monovette, Sarstedt, Germany). Analysis of HbA_1c_ and lipids were conducted by the Department of Clinical Biochemistry, Addenbrooke’s Hospital, Cambridge; analysis of plasma vitamin C and serum fructosamine were conducted by the National Institute for Health Research Biomedical Research Centre’s Core Biochemistry Assay Laboratory, Cambridge. Both laboratories are fully accredited to perform biochemical analyses.

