## Methods/Design

### Study design

*Get Moving* is a parallel group, open label, randomised controlled trial with allocation of 488 participants to either no intervention (control group) or to one of three intervention groups: self-monitoring using paper-based diaries (diary group), activity band with web-based feedback (activity band group), or activity band with web-based feedback plus online coaching engine (activity band plus group). The co-primary outcomes are: (1) PAEE measured using individually calibrated combined heart-rate and movement sensing [22,23], and (2) cardiorespiratory fitness measured using heart rate response to a sub-maximal treadmill exercise test. The secondary outcomes are: anthropometric measures (body mass index (BMI), body fat %, weight and waist circumference), blood pressure, plasma vitamin C levels, biochemical measures (HbA_1c_, fructosamine, cholesterol and triglycerides), Short Form 8 (SF-8) health survey questionnaire, theory of planned behaviour (TPB) measures, perceived stress, self-monitoring behaviour and self-reported recent physical activity (RPAQ). Ethical approval was obtained from Cambridge Central NHS Research Ethics Committee (Ref 09/H0308/3). The design of the trial and flow of participants are shown in Figure 1.

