#### Statistical analysis

Baseline characteristics of the study population will be summarised separately within each randomised group. The co-primary outcomes, PAEE and cardiorespiratory fitness, will each be analysed using an ANCOVA that includes all participants in the group to which they were randomised, regardless of the intervention actually received (Intention-to-Treat analysis). The outcome in the ANCOVA model will be change (follow-up minus baseline) in PAEE (cardiorespiratory fitness), with the baseline value included as a covariate in the model. For each outcome a 3 degrees of freedom test will be performed of the null hypothesis that there is no difference between the 4 randomised groups. The ANCOVA model will also be used to derive estimates of the differences in mean change and 95% confidence intervals for each of the 6 pairwise comparisons: ‘*Diary*’ vs. ‘*Control*’, ‘*Activity Band*’ vs. ‘*Control*’, ‘*Activity Band Plus*’ vs. ‘*Control*’, ‘*Activity Band*’ vs. ‘*Diary*’, ‘*Activity Band Plus*’ vs. ‘*Diary*’ and ‘*Activity Band Plus*’ vs. ‘*Activity Band*’. Where baseline values of the outcome are missing, the missing indicator method will be used to enable these participants to be included in the analysis [40]. An analysis will be performed to check whether adjusting for age, sex and BMI (the randomisation stratifiers) in the ANCOVA model has any impact on the conclusions; if it has no impact, then they will not be included in the model.

For each continuous secondary outcome, the 6 pairwise differences between randomised groups will be estimated, together with 95% confidence intervals, using ANCOVA as described previously. Any continuous endpoints whose distribution is skewed will be log transformed prior to analysis, in which case a ratio of geometric means (and confidence interval) will be reported.

Subgroup analyses by sex and BMI (below/above median value) will be investigated for the 2 co-primary outcomes only.

Degree of use of the intervention will be summarised separately within each intervention group (i.e., the Diary, Activity Band and Activity Band Plus groups). The numbers and types of adverse events within each randomised group will be reported.

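### HbA1c and lipids changed analyser mid-trial and the ANCOVA has no analyser term: the group differences stay unbiased, but a cheap factor would recover a little precision

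*Protocol article*

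**What the plan says.** The Biological measures section gives the instruments. HbA1c "was analysed in fresh blood by ion-exchange high-performance liquid chromatography", using the "Tosoh G7 Haemoglobin Auto-analyser before August 2013 and Tosoh G8 Haemoglobin Auto-analyser after". Total, LDL and HDL cholesterol and triglycerides were also measured in fresh blood, on the "Dimension RxL Max Clinical Chemistry System (Siemens Healthcare Ltd) before December 2013 and Advia 2400 Chemsitry System (Siemens Healthcare Ltd) after". On laboratory quality it adds only this: "Both laboratories are fully accredited to perform biochemical analyses". It mentions no comparison or conversion between old and new instruments.

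Study design lists these measures among the secondary outcomes. For them, Statistical analysis states: "For each continuous secondary outcome, the 6 pairwise differences between randomised groups will be estimated, together with 95% confidence intervals, using ANCOVA as described previously". The model referred to takes follow-up minus baseline as the outcome, "with the baseline value included as a covariate in the model". Age, sex and BMI are kept only if they alter the conclusions. No analyser or calendar-period term is named.

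**The concern.** Two instruments measuring the same analyte need not agree exactly, and accreditation does not show that they do. Because samples were assayed fresh, a participant's two results come from whichever instrument was in service at each visit. With baseline before a switch and follow-up after it, any offset between instruments becomes part of that participant's change.

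Baseline adjustment does not fully remove the offset for later participants either. When both samples are on the new instrument, the offset raises both values, but the regression on baseline takes out only a fraction of it. The stated model pools all three kinds of participant and charges the differences between them to residual error. What is at stake is the precision of the HbA1c and lipid comparisons.

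**Working it through.** **The plan's own figures.** The article gives none for HbA1c or lipids. Its sample-size figures concern only the co-primary outcomes, and they reproduce. With 100 per group, two-sided 5% and 80% power (1.960 + 0.842 = 2.802):

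- PAEE: 0.076 × √(1 − 0.58²) × 2.802 × √(2/100) = 0.0245 kJ/kg/min (stated 0.025).
- Fitness: 1.0 × √(1 − 0.88²) × 2.802 × √(2/100) = 0.188 L/min (stated 0.19).

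Neither depends on the analysers.

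**Assumptions, because the documents are silent.** Work in units of the between-person SD.

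- Offset d = 0.1 to 0.5.
- Share straddling a switch p = 0.05 to 0.20. With even accrual and about 12 weeks between visits, this corresponds to accrual over 12/0.20 = 60 to 12/0.05 = 240 weeks.
- Baseline-to-follow-up correlation r = 0.6 to 0.8.

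**Where the offset goes.** Regressing change on baseline is the same as regressing follow-up on baseline with slope r, approximately. The part of the offset left over is:

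- old/old: 0
- old/new: d
- new/new: d − r·d = (1 − r)d, that is 0.2d to 0.4d

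Three levels are therefore needed, not just a flag for straddling.

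**Residual variance without the term.** Let q be the share of baselines after the switch, so that q + p is the share of follow-ups after it. Then:

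- V_f = 1 + d²(q + p)(1 − q − p)
- V_b = 1 + d²q(1 − q)
- C = r + d²q(1 − q − p)
- residual variance = V_f − C²/V_b, against 1 − r² with the analyser pair in the model

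Worst corner of the range, with the switch at mid-accrual (q = 0.5), r = 0.8, p = 0.20, d = 0.5: V_f = 1.0525, V_b = 1.0625, C = 0.8375. The residual variance is 1.0525 − 0.7014/1.0625 = 0.3924, against 0.36. The ratio is 1.090, and its square root is 1.044.

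| r | p | d | SE larger by |
|---|---|---|---|
| 0.6 | 0.05 | 0.1 | 0.05% |
| 0.8 | 0.10 | 0.2 | 0.4% |
| 0.6 | 0.20 | 0.5 | 2.3% |
| 0.8 | 0.10 | 0.5 | 2.7% |
| 0.8 | 0.20 | 0.5 | 4.4% |

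The position of the switch matters little: in the worst corner, q = 0.1 gives 5.3% and q = 0.8 gives 3.4%.

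**Cost of the term.** With 17% loss, 488 × 0.83 ≈ 405 participants remain. Residual degrees of freedom fall from 400 to 398, and the standard error rises by at most about √(1 + 2/398) − 1 = 0.25%. The net gain is therefore about zero at the low end and roughly 4% at the high end.

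**Simulation of the planned analysis** (488 participants, 8 strata, blocks of 8 over four arms, 17% random loss, offsets 0.2 to 0.5 SD, 1,500 runs per setting):

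- Without the analyser terms, bias in a between-group difference was −0.005 to +0.005 SD, which is simulation noise. Type I error was 4.1 to 5.1%.
- With them, bias was again about zero and type I error 4.2 to 5.8%.
- The estimates' actual spread was 0 to 2.1% larger without the terms. A repeat run with offsets from 0.1 to 0.5 SD put the model-based standard error, which sets the reported confidence interval, about 0 to 4% higher. The spread grows less because blocking already balances part of the nuisance, while the model still counts all of it as residual error.

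**The case against.** The strongest reply is that nothing in the plan is wrong. Allocation was concurrent, in blocks of 8 within strata, and follow-up was at about 12 weeks in every group. The offset is therefore unrelated to arm and cancels in expectation. An ANCOVA without an optional precision covariate is still valid. **This stands.**

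A reader might infer that the switch biases the treatment contrasts through chance imbalance in straddling. That does not follow. With p = 0.15 and 100 per arm, the SD of the difference in straddling share under simple randomisation is √(2 × 0.15 × 0.85/100) = 0.05. A five-point gap is an ordinary draw, and the confidence interval already allows for it. Bias would need loss or visit timing that differs by arm around a switch, which the documents do not suggest.

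A reader might also infer that reported within-arm changes are distorted. Raw mean change in an arm would move by about p × d (0.01 to 0.10 SD over the simulated range), nearly equally in every arm. Statistical analysis, however, plans between-group differences and no within-group estimate or test.

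It can further be said that the offset may be negligible, which is possible, and that such detail belongs in an analysis plan that is not shown. The second point stands in part. The article itself fixes the covariates for these outcomes and itself discloses the switches, so the mismatch is visible in the text. It does not rule the adjustment out, though, and if the full plan already includes it, this point falls away.

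**Conclusion.** This is a small, conditional loss of precision on HbA1c and the lipids, not an error in the plan. Both analysers changed, and the stated model has no term for either change. If an offset exists, some of it becomes residual variance that two degrees of freedom would remove.

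The loss is roughly 0 to 4% of the standard error for offsets of 0.1 to 0.5 SD, 5 to 20% straddling and correlations of 0.6 to 0.8. All three ranges are assumptions: the documents give no offsets, accrual dates or straddling counts. They support no claim that the six between-group differences are biased, that type I error is inflated or that any conclusion would change.

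**What to change.** For HbA1c, and separately for total, LDL and HDL cholesterol and triglycerides, add a three-level factor to the ANCOVA: both samples on the old analyser, baseline old and follow-up new, both new. Assign it from the two sample dates, using August 2013 for HbA1c and December 2013 for lipids, with the laboratory's exact changeover day. Fix this before the between-group analysis is run.

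If the laboratory holds a documented conversion between instruments, put results on one scale first and keep the factor as a check. The factor removes a constant offset; for an outcome analysed on the log scale, it removes a proportional one.

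The cost is two degrees of freedom per model. Sample dates should already be held, and no new data are needed. If the offset is negligible, nothing is gained and almost nothing is lost.
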